## Definition and Management of Symptomatic and Asymptomatic Malaria

### Definitions of Symptomatic and Asymptomatic Malaria for Research Purposes

The following exhibit describes the definitions of clinical episodes of malaria (symptomatic cases) and asymptomatic malaria this study will use. The definitions of symptomatic malaria are listed in decreasing order of specificity. Note that the Primary Case Definition (temperature 37.5ºC in the simultaneous presence of a density of asexual stage *P. falciparum*  50,000 parasites/μl blood) is the third most specific of the definitions. We have chosen it as the primary endpoint because it is quite specific and we expect enough cases to occur under that definition to yield adequate power for the study.

All of the case definitions may present in this study through either active or passive case detection.

| Exhibit 8. Malaria Case Definitions | | | |
| --- | --- | --- | --- |
| **Definitions of Clinical Cases of Malaria** | | | |
| ***Name*** | ***Fevera*** |  | ***Parasite densityb*** |
| Secondary Case Definition (200) | 37.5ºC | ANDc | 200K |
| Secondary Case Definition (100) | 37.5ºC | AND | 100K |
| **Primary Case Definition** | **37.5ºC** | **AND** | **50K** |
| Secondary Case Definition (10) | 37.5ºC | AND | 10K |
| Secondary Case Definition (0) | 37.5ºC | AND | >0 |
| Secondary Case Definition (0*) | 37.5ºC OR history of fever in the last 24 hrs | AND | >0 |

| **Definitions of Asymptomatic Malaria** | | |
| --- | --- | --- |
| ***Name*** | ***Description*** | ***Parasite densityb*** |
| Infection Definition | Episode of malaria infection | >0 |
| Infection above 50K | Parasite density > 50K | 50K |

1. Fever is documented axillary temperature.
2. Asexual stage *P. falciparum* parasites/μl blood; K denotes thousands.
3. AND means “simultaneous presence of.”

### Definition of Symptomatic Malaria for Clinical Purposes

In the event that a subject presents to the WRP KC with fever (≥ 37.5ºC), history of fever during the past 24 hours, or any complaints that the attending clinician suspects are due to malarial infection, an MBF will be taken and read immediately to confirm the diagnosis, and a CBC will be performed. All subjects with asexual parasitemia will then be treated with antimalarials as indicated in Section 7.3.3.

Subjects found to meet any of the above criteria through active case detection will be evaluated by MBF and treated the same day, if appropriate.

### Management of Symptomatic Malaria during the Study

In April 2004, the Kenyan Ministry of Health announced artemether/lumefantrine (*Coartem***/***Riamet*) as the new treatment-of-choice of non-severe malaria in all age groups; the new MoH guidelines are in preparation. *Coartem* will be used for treatment of children who acquire uncomplicated malaria during the study. This drug has been shown to be safe and effective in children in Africa (35). Artemether/ lumefantrine will be administered as a six-dose regimen over 60 hours in accordance with the scheme outlined in Exhibit 9. This is the dosage regimen the WHO recommends for use in malaria endemic areas such as Kenya. The six-dose regimen has been found to be efficacious in Kenyan children under five years old (36).

Exhibit 9. Artemether/Lumefantrine (*Coartem*/*Riamet*) Dosing Schedule

| **Body weight (Kg)** | **Number of tablets* at 0, 8, 24, 36, 48, and 60 hours** |
| --- | --- |
| 5 to 14.9 | 1 |
| 15 to 24.9 | 2 |
| 25 to 35 | 3 |

*Each tablet contains 20 mg of artemether and 120 mg of lumefantrine

In addition to artemether/lumefantrine, and in the unlikely event of treatment failure with that drug combination, the following regimen will also be available at the WRP KC as an alternative for the treatment of uncomplicated malaria:

- *Malarone* Pediatric Tablets (atovaquone 62.5 mg and proguanil Hcl 25 mg) dosed according to the body weight schedule presented in Exhibit 10.

**Exhibit 10.** ***Malarone* Dosage for Treatment of Acute Uncomplicated Malaria in Pediatric Patients**

| **Weight (kg)** | ***Malarone* Pediatric Tablets**: **Total Daily Dosage** | **Dosage Regimen** |
| --- | --- | --- |
| 11-20 | 250 mg/100 mg | 4 *Malarone* Pediatric Tablets as a single dose daily for 3 consecutive days |
| 21-30 | 500 mg/200 mg | 8 *Malarone* Pediatric Tablets as a single dose daily for 3 consecutive days |
| 31-40 | 750 mg/300 mg | 12 *Malarone* Pediatric Tablets as a single dose daily for 3 consecutive days |
| >40 | 1 g/400 mg | 16 *Malarone* Pediatric Tablets as a single dose daily for 3 consecutive days |

For subjects of < 11 kg body mass, the following regimen will also be available at the WRP KC as an alternative for the treatment of uncomplicated malaria:

- Quinine: Standard oral course of quinine 10 mg/kg t.i.d. for 7 to 10 days.

Children with manifestations of severe malaria (see Section 16.6; Appendix F) will be treated with parenteral quinine, 15 mg/kg loading dose followed by 10 mg/kg, q12 hours. Intravenous quinine will be administered in 5% dextrose. Other antimalarials (e.g. IM artemether) may be used at the physician investigator’s discretion should clinical circumstances dictate. Subjects with uncomplicated malaria and persistent vomiting, particularly those who are observed to not retain oral medication, should receive parenteral antimalarials. All subjects requiring parenteral treatment will be treated under observation at Kombewa Clinic or admitted to a referral hospital. At the investigator’s discretion, definitive clinical management may need to be rendered at the New Nyanza Provincial General Hospital (NNPGH), Kisumu, Kenya. A clinical member of the study team will review any such subject admitted to NNPGH each day until discharge. (See SOP 501.02: “Referral of Study Subjects at the WRP Kombewa Clinic for Medical or Dental Care”.)

All study subjects treated for malaria will be followed (at the clinic or by field worker home visit) until resolution of symptoms. All treatment courses will be administered under the direction of the attending clinician and recorded in the subject’s record. Subjects found to have clinical malaria will be treated before any further immunization. Subjects evaluated in this manner will be given the appropriate dose of vaccine if their clinical symptoms resolve within the vaccination window. If the clinical symptoms do not resolve within that period, the subject will not be vaccinated; however, the subject will be followed for collection of all study data points.

# SAMPLE HANDLING and ANALYSIS

## Overview of Collection Time Points

Blood will be collected from subjects for study purposes by venipuncture up to 15 times during the study. The maximum amount of blood requested from any subject for standard collection over the study duration should not exceed 30 ml. Additional blood may be obtained as deemed necessary by one of the investigators or clinicians to evaluate any illness or condition. Specimens collected during the study will be stored under the conditions specified within this protocol at either the laboratories within WRP-Kisumu or the WRAIR Department of Immunology. Only the investigators, laboratory managers and their staff will be permitted access to the specimens.

***Safety***

Testing for CBC, creatinine, and ALT at Visit #1 (Screening Period: Days -45 to 0) and at Visits # 2, 7, 12, and 17 (approximately Study Days 0, 29, 57 and 85).

Testing for hemoglobinopathies (sickle cell disease/trait, G6PD deficiency and alpha-thalassemia) will be performed at Visit 1 (Screening Period: Days -45 to 0).

***Malaria Blood Films (MBFs)***

MBFs for baseline and efficacy evaluation of parasite densities will be performed, commencing on screening days, continuing on vaccination days (Visits 2, 7, 12 o/a Study Days 0, 29, and 57), and every month thereafter, at the WRP KC. (For specific monthly dates, see Section 7.2).

The procedures for MBFs are outlined in the following WRP KC SOPs:

SOP KCL 301: Malaria Blood Films – Blood Sample Reception andSmear Preparation

SOP KCL 302: Preparation of Buffer Solution

SOP KCL 303: Preparation of Working Giemsa and Staining

SOP KCL 304: Slide Coordination and MBF Results Interpretation

SOP KCL 305: Malaria Blood Films – Reading and Quantification of Malaria Parasites

SOP KCL 306: Malaria Blood Films – Documentation and Storage of MBFs

SOP KCL 307: Malaria Blood Films – Quality Control and Quality Assurance

SOP KCL 003: Finger-Prick for blood Smear

SOP KCL 008: Processing of Laboratory Blood Specimens

SOP KCL 012: pH meter Calibration

SOP KCL 017: Microscope Maintenance

***Serology***

Separation of serum/plasma from the venous blood will be performed at the WRP KC and serum samples (approximately 0.5-1.0 ml) will be aliquoted for later use to determine anti-MSP-1 antibody levels at Visits 2, 7, 12, and 17 (approximately Study Days 0, 29, 57 and 85) and every three months (Visits 20, 23, 26) thereafter until the conclusion of the study.

## Handling of Biological Samples Collected by the Investigator

### Instructions for Handling of Serum Samples

*Collection*

Venous whole blood will be collected under appropriate aseptic conditions. Serum will be collected whenever possible using Vacutainer tubes with integrated serum separator (e.g., Becton-Dickinson *Vacutainer*SST or *Corvac* Sherwood Medical). The blood will be mixed immediately by inverting the tube five times in order to mix the blood with the clot activator.

*Serum Separation*

- The clot will be allowed to set for 45 to 60 minutes at room temperature. Thereafter, the tubes will be centrifuged at 1500 g for 10 minutes.
- Following separation, the serum will be transferred to the appropriate standard screw top cryovials using a disposable pipette. The serum will be transferred as gently as possible to avoid blood cell contamination.
- The cryovials will not be overfilled (max. 3/4 of the total volume) to allow room for expansion upon freezing.
- The tube will be identified by an appropriate cryo-resistant label.

### Labeling

- Standard cryolabels will be used to label each serum or blood sample. In addition to a barcode, each label will contain the KEMRI SSC number, WRAIR protocol number, the SID number, and the date of collection.
- Any hand-written additions to the labels must be made using indelible ink.
- To ensure optimal attachment of the label, it should be attached to the tube as follows:
  - First attach the blank end of the label to the tube
  - Wrap the label around the tube so that the opposite end of the label overlaps the blank end ensuring that no written portion is covered
- Labels should not be attached to caps.
- The tubes of serum should be stored in a vertical position at a temperature  -50°C.

## Laboratory Procedures

The PI and laboratory officer will maintain detailed SOPs governing laboratory assays in the WRP Kombewa Clinic laboratory. The following overview summarizes the methods that will be used.

### Hematology

Complete blood counts (CBCs) will be measured at regular intervals throughout the study period. The PI and WRP KC senior lab supervisor will ensure performance of laboratory reference value checks and will provide documentation to the study monitor before study start.

### Biochemistry

Renal (creatinine) and liver (ALT) function tests will be measured at regular intervals throughout the study safety period. The PI and WRP KC senior lab supervisor will ensure performance of laboratory reference value checks and will provide documentation to the study monitor before study start.

### Hemoglobinopathies

Assays for detection of sickle cell disease (SS) or trait (SA), G6PD deficiency, and alpha-thalassemia will be run at screening. The PI and WRP KC senior lab supervisor will ensure performance of laboratory reference value checks and will provide documentation to the study monitor before study start.

### Procedure for the Laboratory Diagnosis of Malaria

Routine MBFs will be collected at all scheduled blood draws. Whenever a child is suspected to have malaria, an acute MBF will be obtained and read immediately. Malaria parasite density will be estimated IAW SOP KCL 304 (See Section 16.3)

(Details for acute MBF preparation and reading are found in SOP KCL 305: Malaria Blood Films – Reading and Quantification of Parasites on Giemsa Stained Slides, Section E.)

### Serology: Antibody Responses assayed with ELISAs

Serological assays for antibody determination will be performed at the WRP-Kisumu laboratories and will undergo QC at the WRAIR. Blood will be collected at Visits 2, 7, 12, 17, 20, 23, and 26 (o/a Study Days 0, 29, 57, 85, 171, 256, and 340) from each subject and processed as detailed in Section 8.2.1. All blood samples will be labeled with the KEMRI SSC number, WRAIR protocol number, the SID number and the date the sample was obtained.

Immunogenicity (antibody levels) will be determined by evaluating antibody (IgG) responses to the *P. falciparum* MSP-142 as measured using standard ELISA methodologies with appropriate capture antigens. (Details of this ELISA procedure are found in SOP No. KSM 201.1: SOP for Validation and QC of 3D7 MSP-42 Human ELISA and SOP No. KSM 202.0: SOP for Test Samples of 3D7 MSP-42 Human ELISA.)

*i. ELISA to measure immunogenicity against MSP-142 (3D7):*

Primary analysis will be performed at USAMRU-K in Kenya, in the laboratory of Dr. [name].

Secondary analysis will be performed at the WRAIR, in the Malaria Serology Laboratory, to ensure quality assurance/quality control, under the direction of [name].

For the analysis of MSP‑142-specific antibody titers, an ELISA will be performed according to an established and validated standard operating procedure. Induction of humoral immunity will be measured using MSP‑142 (3D7) (Lot # 0649) as the capture antigen. Pre-immune and immune sera following each vaccine dose will be analyzed for the induction of MSP‑142-specific antibody titers. Antibodies will be measured following secondary antibody conjugate with anti-human IgG horseradish peroxidase (HRP) incubation with the HRP substrate ABTS. Absorbance will be measured after 60 minutes at 405 nm with a microplate reader (Molecular Devices, Spectra-max Plus 384 using SoftMax Pro software). The antibody titer will be calculated as the serum dilution that produced an absorbance of one optical density unit in the ELISA assay.

*ii. ELISAs to measure immunogenicity against fragments of MSP-1 (3D7, FVO, CAMP) (MSP-142, MSP-119, and MSP-1-Domain 2):*

Assay will be performed at the WRAIR, in the laboratory of [name] and [name].

The C-terminal fragment of MSP‑142 is highly conserved and constrained with six disulfide bridges. The p19 fragment is organized into two tandem EGF-like domains designated "EGF-domain 1" and "EGF-domain 2". Previous data show that mAbs that inhibit parasite invasion in vitro and inhibit the secondary processing of MSP‑142 bind to p19 on either EGF-domain 1 (mAb 12.8) or to an epitope formed through double-domain (p19) (mAb 12.10). Pre-immune and immune sera obtained following each vaccine dose will be analyzed for the induction of antibody specificities induced to fragments of MSP‑1 by ELISA using six capture antigens, either homologous with the 3D7 vaccine strain, or the heterologous FVO and CAMP strains: full-length *E. coli*- MSP‑142, C-terminal MSP‑119 (p19), and -EGF-like domain 2 (EGF2). For the analyses comparing MSP‑142-fragment-specific antibody titers, ELISA wells will be coated with equimolar concentrations of each antigen. Following incubation with immune sera, antibody titers will be measured using anti-human IgG, (H+L)-alkaline phosphatase (AP) conjugate followed by development with AP substrates, p-nitrophenol phosphate (Sigma) in diethanolamine. Absorbance will be measured after 30 minutes at 405 nm using a Molecular Devices, Spectra-max Plus 384 using SoftMax Pro software. The antibody titer will be calculated as the serum dilution that produced an absorbance of 1 optical density unit in the ELISA assay.

*iii. Competition ELISAs:*

Assay will be performed at WRAIR, in the laboratory of [name] and [name].

This assay has been previously described (38).

Immune sera from volunteers vaccinated with FMP1/AS02A will be evaluated to determine their ability to compete for binding to recombinant MSP‑142 using a panel of monoclonal antibodies (mAbs) having known functional antibody specificities, i.e. growth invasion/inhibition activities (i.e., mAbs 12.10, 12.8). The competition ELISA is based on the hypothesis that serum antibodies that share overlapping epitope specificities with mAbs bind close to the mAbs and therefore sterically interfere with mAb binding. The degree of competition is influenced by the relative affinities of the serum antibodies and the mAbs, the degree of overlap of epitopes, and the concentration of antibodies in the serum.

iv. Inhibition of MSP-142 Secondary Processing:

Assay will be performed at the WRAIR, in the laboratory of [name] and [name].

This assay has been described previously (39).

A target of protective immunity is the induction of antibody specificities to inhibit secondary processing of MSP1 to a membrane-bound fragment (MSP-119) and a soluble fragment (MSP-133). Therefore, the secondary processing is a pre-requisite for merozoite invasion and antibodies that block this processing also inhibit invasion.

Merozoites released from the *P. falciparum* 3D7, FVO or CAMP strains will be isolated and prepared for evaluation with immune sera for their ability to inhibit the secondary processing of MSP-142 to p19 and p33. The merozoite pellet is suspended in ice cold PBS (Ca+2 and Mg+2 free) containing leupeptin, antipain, and aprotinin at 10 mg/ml and TLCK at 100 M and washed three times in this same buffer. The merozoites are suspended in the same buffer supplemented with 1 mM CaCl2 and 1 mM MgCl2, and distributed in aliquots of 2x109 merozoites in 1.4 ml microfuge tubes and pelleted at 12,000 x g for 2 min. Pellets are suspended in 30 l of ice cold PBS supplemented CaCl2, MgCl2 and the immune sera from vaccinees. Assay controls include: 1 mM PMSF (inhibits secondary processing); no addition (permits secondary processing to proceed); and no addition followed by immediate addition of SDS (time zero control). All samples are incubated in a water bath at 37oC for 1 hour. Reactions are stopped by addition of SDS, followed by electrophoresis and analysis by western blotting for production of p33. Processing is detected by reaction with biotinylated-rabbit p42 polyclonal sera.

### Growth Inhibition Assay (GIA)

Invasion/Growth Inhibition Assays (i.e., measurement of invasion inhibitory antibody responses by parasite-derived lactate dehyrodrogenase assay [pLDH]) will be performed at the WRAIR using the pLDH method.

This assay will be performed at the WRAIR, in the laboratories of [name], [name], and [name].

Sera will be evaluated for inhibition of malaria parasite invasion/growth by measuring lactate dehydrogenase levels in late trophozoite stage *P. falciparum* adapted from a method developed by Prudhomme and Sherman (40). 3D7, FVO and CAMP strain *P. falciparum* are synchronized by thermal cycling as described by Haynes and Moch and collected for use at the beginning of schizogony (41). Cultures are adjusted to 0.3% parasitemia with type A human erythrocytes and assays are conducted in a final hematocrit of 1%, with test serum concentrations ranging from 5 to 20%. Assays with 3D7, FVO, and CAMP strains of *P. falciparum* will be collected 40 hours or 46 hours, after initiation. Parasite invasion inhibition is calculated as follows:

% Inhibition = [(ODimmune serum  ODRBC)  (ODpre-immune serum  ODRBC)] × 100

### Genotyping

Anticoagulated whole blood will be collected in heparin or EDTA as per schedule detailed in Exhibit 7 for purposes of genotyping the molecular allele of MSP-1 and determination of multiplicity of infections. Approximately 200 µl whole blood will be collected and processed for DNA by Qiagen whole blood method as described by manufacturer. DNA will be stored at –70˚C until used for molecular analysis.

*i. MSP-142 Genotyping:*

Anti-coagulated EDTA blood collected at the indicated time points in Exhibit 7 from each subject will be used for DNA preparation. 200 l of whole blood from each subject will used to prepare DNA using QIAamp DNA Mini Kit (Valentia, CA). For back-up, 20 l whole blood will be spotted on *Isocode Stix* (Schleicher and Schuell, Dassel, Germany) in quadruplicate and stored at WRP-Kisumu. The DNA and the spotted blood will be shared on-a-need-basis between WRP-Kisumu and the WRAIR. A single primer set that amplifies a common genetic region in the MSP-1 gene from both the 3D7 (MAD20) allele and the FVO (K1) allele will be performed prior to real-time PCR detection of individual single nucleotide polymorphisms (SNPS). Each DNA sample from each time point will be assessed for the frequency of single or multiple SNPs for each of the eight polymorphisms. Four SNP assays have been developed for the 3D7 allele (vaccine allele), namely the 1) 3D7-33 SNP; 2) E allele; 3) T allele; 4) SR allele. Four SNP assays have been developed for the FVO (K1) allele, namely the 1) FVO-33 SNP; 2) Q allele; 3) K allele; 4) NG allele. As the technology currently stands (2nd quarter 2004) the assay is both sensitive and specific for detection of presence/absence (frequency) of each MSP-142 allele. Assays (real-time PCR, sequencing) that quantitatively measure the proportion of each allele in a sample are under development and may be utilized to quantitatively determine changes in abundance of MSP-1 alleles after vaccination.

*ii. Multiplicity of Infection Genotyping:*

To determine how many different infectious strains of *P. falciparum* the child was infected with, a molecular genotyping method that makes use of a PCR amplification method followed by RFLP (restriction fragment length polymorphism) will be used. Standard methods that measure the frequencies of three *P. falciparum* genes (MSP-1, MSP‑2, GLURP) will be analyzed for determination of multiplicity of infection. This approach will assess whether the FMP1/AS02A malaria vaccine helps to limit the number of infectious strains of malaria with which a child is infected. Further, it will allow us to measure the fitness/vulnerability of these parasite subpopulations, which are present in areas of high transmission.

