### Active and Passive Case Detection of Malaria

*Active case detection* is represented by 1) the 15 scheduled MBF/CBC collections at the clinic and 2) the 13 monthly field worker home visits (see Exhibit 7 and Section 7.2), “Detailed Description of Study Stages and Visits”). All these scheduled sample collections and home visits will be undertaken whether or not children are symptomatic, and will include checks of temperature. All children known to be parasitemic with symptoms, including those with fever (≥ 37.5C) or history of fever will be documented as such and treated as medically appropriate on the same day. The malaria blood films (MBFs) of children who are afebrile and well at the clinic will be read according to a time schedule dictated by microscopist workload. Therefore, any asymptomatic, but parasitemic, children who do not have their MBFs read “in real time” will not receive antimalarial treatment. (It is anticipated that these will represent 80-90% of children during high-transmission months). During field worker visits to the subjects’ homes, any child found to be ill from any cause will be promptly transported by the field worker to the WRP KC for evaluation and appropriate medical management.

*Passive case detection* is represented by subjects’ accessibility to the 12 field stations, which are manned on a 24-hour basis by field workers, as described in Section 16.3.3. Passive case detection will be in effect from the day of screening to Study Day 0 (for all those screened), and from Study Day 0 to study end (for all those enrolled). Parents of subjects will be advised on a continuous basis to bring any ill subject to a field station for immediate transportation to the KC at any time, night or day. Field workers will have standing instructions to arrange transport to the KC for any subject with reported fever or history of fever in the past 24 hours. Thus, all such children will be evaluated with an acute MBF and CBC. Subjects will then be treated at the KC IAW Section 7.3.3 (for malaria), Section 6.3.1 (for other illnesses), clinic SOPs, and established clinic guidelines. (This facility and its staffing are described in detail in Section 7.3.)

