**Days 14 to 354 ± 7 Field Worker Home Visits**

***Field Worker Visits 1-13***

- Monthly field worker home visits will fall o/a Study days 14, 43, 71, 99, 129, 158, 186, 214, 242, 270, 298, 326, and 354 (all ± 7)
- Field workers will take axillary temperatures, solicit history of fever in the last 24 hours, remind parents of appointments and reconfirm their locations
- Any subject with a fever or history of fever in the past 24 hours will be taken to the KC for evaluation, including MBF and CBC.
- Any deaths, out-migrations, absences from Kombewa, and antimalarial usage will be documented
- Parents/subjects will continue to attend the WRP KC whenever the latter are sick
- Check concomitant medications

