### Secondary Endpoints

Because this is a Phase IIb trial, it has many secondary endpoints. Their purpose is to gain insight into the efficacy of the vaccine and to help define a primary endpoint for a confirmatory Phase III trial. They are not intended for use to make formal claims about the vaccine.

Measurements of efficacy during the EFP:

- Times to clinical episode of *P. falciparum* malaria meeting the various secondary case definitions shown in Exhibit 8
- Time to presence of asexual stage *P. falciparum* parasites during the six-month efficacy follow-up period
- Time to parasite density  50,000 asexual stage *P. falciparum* parasites per microliter of blood during the six-month efficacy follow-up period
- Number of clinical episodes of malaria, per subject, meeting the primary case definition
- Presence of MSP-1 3D7 parasites in clinical cases of malaria meeting the primary case definition
- Presence of MSP-1 3D7 parasites at a given cross-section survey time
- Time to anemia defined as Hgb < 8.0 g/dl, whether by active or passive case detection
- Proportion of subjects with anemia (Hgb < 8.0 g/dl)

Safety during the EFP:

- Occurrences of solicited AEs during a seven‑day follow-up period (vaccination day and six subsequent days) after each vaccination (five visits: vaccination day and days 1, 2, 3, and 6)
- Occurrences of unsolicited AEs during a 30-day follow-up period after each vaccination (vaccination day and 29 subsequent days)
- Occurrences of SAEs between the first vaccination and the end of the EFP

Immunogenicity during the EFP:

- Geometric means of MSP-1 Ab titers at Visits 2, 7, 12, 17, 20, and 23 (o/a Study Days 0, 29, 57, 85, 171, and 256)

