#### Biological effects

***Secondary endpoints***

*Time to presence of asexual stage P. falciparum parasites during the six-month efficacy follow-up period* – Similar analyses as those described for the primary endpoint will be performed.

*Time to parasite density  50,000 asexual stage P falciparum parasites per microliter of blood during the six-month efficacy follow-up period* – Similar analyses as those described for the primary endpoint will be performed.

*Presence of MSP-1 3D7 parasites in clinical cases of malaria meeting the primary case definition during the six-month efficacy follow-up period* – Frequencies and percentages of cases with circulating MSP-1 3D7 parasites will be calculated by vaccine study group.

*Presence of MSP-1 3D7 parasites at a given cross-section survey time during the six-month efficacy follow-up period* – For a given survey time, the frequency and percentage of subjects with circulating MSP-1 3D7 will be calculated by vaccine study arm.

*Time to anemia defined as hemoglobin level < 8.0 g/dl during the six-month efficacy follow-up period* - Similar analyses as those performed for the primary endpoint will be conducted. In addition, a Cox model with vaccine study arm, baseline hemoglobin, and age as covariates will be applied to the data. The six-month cumulative incidence rate of anemia will be calculated for each vaccine study arm.

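### The protocol secures no genotyping sample at unscheduled sick visits, so the 3D7-in-cases endpoint would be missing for passively detected cases

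*Protocol*

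**What the plan says.** **Where genotyping blood comes from.** Section 8.3.7 gives the rule twice. In general, "Anticoagulated whole blood will be collected in heparin or EDTA as per schedule detailed in Exhibit 7 for purposes of genotyping". For MSP-1 genotyping in particular, "Anti-coagulated EDTA blood collected at the indicated time points in Exhibit 7 from each subject will be used for DNA preparation".

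**What Exhibit 7 covers.** It is the schedule of routine evaluations. Its 3D7 allotyping row is marked at every scheduled clinic blood draw. It is also marked at field worker visits 1-13, under a footnote that triggers collection when the child has fever or a 24-hour history of fever. There is no column for unscheduled visits.

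**What happens at a sick visit.** For children brought in through passive detection, Section 7.1.4 says "Thus, all such children will be evaluated with an acute MBF and CBC". For any child presenting to the clinic with suspected malaria, Section 7.3.2 says "an MBF will be taken and read immediately to confirm the diagnosis, and a CBC will be performed". Neither mentions allotyping. For febrile children found at home, Section 7.2 says the child "will be taken to the KC for evaluation, including MBF and CBC", without the allotyping that Exhibit 7 marks for the same children.

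**What the endpoints need.** Section 12.1.2 lists the secondary endpoint "Presence of MSP-1 3D7 parasites in clinical cases of malaria meeting the primary case definition". Section 12.4.2 plans its analysis as follows: "Frequencies and percentages of cases with circulating MSP-1 3D7 parasites will be calculated by vaccine study group". Section 12.1.3 adds a tertiary endpoint on allele types per malaria episode. Section 7.3.1 states that all case definitions may be met through active or passive detection.

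**The concern.** An endpoint counted over clinical cases needs a parasite DNA sample from each case, taken during the episode. The sampling rule in Section 8.3.7 points to a schedule of routine contacts, while cases also arise when a sick child is brought in between those contacts. Such a child is filmed and, if parasitemic, treated. Blood from the next scheduled visit is post-treatment and does not describe the parasites behind the episode. A sample not taken at presentation therefore cannot be recovered later, and no analysis plan can repair the gap.

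If the text is followed literally, the case-level allele data would come only from cases that happen to fall on a scheduled contact. Section 4.2 makes the development path, when clinical efficacy is absent, depend on whether parasitemia due to vaccine-homologous strains is reduced. Allele data from clinical cases bear on that question, although they are not the only source.

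**Working it through.** **1. The provisions side by side**

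| Type of contact | Film and CBC | 3D7 allotyping |
| --- | --- | --- |
| Scheduled clinic draw | Exhibit 7 | Exhibit 7 |
| Home visit, child febrile or with fever history | Exhibit 7 footnote; Section 7.2 | Exhibit 7 footnote; not named in Section 7.2 |
| Unscheduled sick visit | Sections 7.1.4 and 7.3.2 | Not named anywhere |

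The third row is the gap. The second row is an internal inconsistency.

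**2. The plan's own figures, used only for the expected number of cases**

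Section 12.3 gives 200 per arm, 20% dropout during immunization, 50% six-month incidence in the comparator arm and a 38% hazard reduction.

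- Hazard: ln 2 / 6 = 0.1155 per month, as stated.
- Incidence in the test arm: 1 − exp(−0.1155 × 0.62 × 6) = 0.349.
- Expected first cases: 160 × (0.500 + 0.349) = about 136, that is 80 and 56 by arm.
- Schoenfeld power: Φ(√(135.9/4) × |ln 0.62| − 1.96) = Φ(0.826) = 0.796, which agrees with the stated rough 80%.

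No stated figure is in dispute.

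**3. Share of cases that coincide with an allotyping contact**

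Inputs from Section 7.2, within the 169-day efficacy follow-up period (SD 71-240):

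- clinic visits on SD 85, 115, 143, 171, 200 and 228 (6);
- home visits on SD 71, 99, 129, 158, 186 and 214 (6).

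Two assumptions are not in the documents: a febrile window of d days before treatment, and onset uniform over the period. Gaps between contacts are 13 to 16 days, so for d up to 13 no window covers two contacts, and the share is about k × d / 169. With k = 12 every contact counts. With k = 11 the SD 71 contact is dropped, because it lies on the boundary and an onset inside the period cannot precede it. A simulation on the nominal days gives the k = 11 column to within 0.1 percentage point.

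| d (days) | 12d/169 | 11d/169 |
| --- | --- | --- |
| 1 | 7.1% | 6.5% |
| 2 | 14.2% | 13.0% |
| 4 | 28.4% | 26.0% |
| 5 | 35.5% | 32.5% |
| 7 | 49.7% | 45.6% |
| 8 | 56.8% | 52.1% |
| 10 | 71.0% | 65.1% |

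The share reaches one half at d = 169/24 = 7.0 days or d = 169/22 = 7.7 days, depending on how the boundary contact is treated.

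**4. In numbers of cases**

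For d of 1 to 4 days, 7.1% to 28.4% of about 136 first cases is roughly 10 to 39 cases over both arms. If every acute film carried a DNA sample, all 136 would be covered.

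**The case against.** The strongest reply is that silence is not exclusion. Exhibit 7 has no sick-visit column for films or CBCs either, yet both are taken. Section 7.2 omits allotyping for febrile children at home visits even though Exhibit 7 requires it, so the narrative sections are an unreliable guide to what is drawn. The Exhibit 5 footnote lists genotyping among the purposes of the efficacy periods, Section 8.1 allows additional blood during illness, and Appendix C lists procedures on allotyping and on malaria diagnosis whose contents are not shown. Nothing forbids using part of the CBC blood for DNA.

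Much of this stands. A reader might infer that the endpoint cannot be derived, or that no DNA will exist for passive cases. The documents do not support that: they fail to provide for the sample, but they do not rule it out. The reply still does not close the gap. Acute films and CBCs have their own explicit instruction outside Exhibit 7 and genotyping has none. Section 8.3.7 names Exhibit 7 as its source twice. The extra blood in Section 8.1 is for evaluating illness.

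On size, a reader might infer that up to 96% of cases are lost, by counting clinic visits alone with a one-day window (6/169 = 3.6% covered). That ignores the fever-triggered allotyping at home visits. With all 12 contacts and windows of 1 to 4 days, the uncovered share is 72-93%, and it is still assumption-based. The visit windows (±14 days for the clinic, ±7 for home visits) do not by themselves change the calculation if visit dates are independent of illness. If a sick presentation may count as the monthly visit, coverage would rise, and the protocol does not say.

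On importance, a reader might infer that the development decision in Section 4.2 loses its evidence. That rule concerns parasitemia due to vaccine-homologous strains, and the separate secondary endpoint of 3D7 parasites at cross-sectional surveys is sampled at every scheduled draw. The affected secondary endpoint is descriptive, and Section 12.1.2 says secondary endpoints are not meant for formal claims.

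**Conclusion.** The point holds as a gap between a stated sampling rule and a stated endpoint. Followed as written, the protocol secures no genotyping sample for passively detected primary-definition cases, so the 3D7-in-cases secondary endpoint and the allele-types-per-episode tertiary endpoint would be missing for them.

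Those cases are plausibly the majority, but this is a judgement and not a figure in the document. It rests on a febrile window shorter than about a week and on uniform onset. A short window fits the design, which staffs field stations around the clock near subjects' homes and arranges transport to the clinic at any hour.

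The primary endpoint, power, safety and the cross-sectional 3D7 endpoint are untouched. Severity is moderate: the loss is confined to descriptive secondary and tertiary endpoints, but it is irreversible once a case has been treated and it is easy to prevent.

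**What to change.** - In Sections 7.1.4, 7.3.2 and 8.3.7, state that whenever an acute film is taken, about 200 µl of EDTA blood from the CBC sample is kept for 3D7 allotyping, drawn before antimalarial treatment.
- Add an unscheduled-illness column to Exhibit 7 with film, CBC and 3D7 allotyping marked.
- Align the field worker visit text in Section 7.2 with the Exhibit 7 footnote that already requires allotyping for febrile children.

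The cost is amendment wording plus DNA preparation and PCR for acute cases, which the endpoints already presuppose. No additional needle stick should be needed, since a CBC is drawn at these visits. At the monthly clinic visits the protocol already takes film, CBC and allotyping from one 1 ml sample. The change is worth making before the first dose, because samples missed at presentation cannot be replaced.
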